### Data management

The collected data will be recorded in a hand-registered logbook and typed in EXCEL, archived in
Google Drive. The Cold Sensitivity Severity Scale and Pain Disability Index questionnaires are applied to each participant in the last evaluation by the hand surgeon to be answered individually and, at the end of the collection, are imported in excel format and archived in Google Drive. All data will be entered manually and electronically and stored on a password-protected laptop, computer hard drive, and external storage device in possession of the responsible for search and virtually shared with the supervisor researcher. Participant files will be stored in numerical order and stored in a secure and accessible place and manner. Participant files will be maintained in storage for a period of 5 years after completion of the study.

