**Figure 1. f1:**
[figure not shown]
Flow chart of the study based on CONSORT criteria.

Following surgery, both groups will additionally receive 1 hour of either electrical stimulation (group A) or sham (group B). In total, two silicone-carbon and gel electrodes (measuring 1 × 1 cm) will be used for all participants, with one placed exactly proximal and the other exactly distal to the surgical site. The two groups will receive the following therapeutic regimens:
•
*Group A: Surgery + PES.* The electrodes will produce a square-pulsed, biphasic, symmetrical current at a frequency of 20 Hz, pulse width of 0.4 ms, and amplitude at the motor threshold of the median nerve, for 1 hour directly after surgery (n = 16);•
*Group B: Surgery + sham PES.* The electrodes will produce a square-pulsed, biphasic, symmetric electric current at a frequency of 20 Hz, pulse width of 0.4 ms, and amplitude at the motor threshold of the median nerve, for 1 hour directly after surgery (the same as Group A) but the electrostimulator will be turned on only until the patient is aware of it, after which the amplitude will be set to zero (n = 16).

In the first post-operative review, the patient will be evaluated by the doctor at the outpatient clinic. A physiotherapist specialized in the area and blinded to the intervention will guide on the rehabilitation protocol that will be monitored remotely by electronic means available to the patient (WhatsApp, Skype, etc.). Patients will undergo a hand sensory re-education protocol based on the one proposed by
Dellon & Jabaley (1982) for a period of 3 months. This protocol involves exercises for discrimination of static and dynamic touch and objects of different shapes, sizes, and textures guided by the physiotherapist, and the patient is also stimulated to perform a home program exercises. This will involve a total of 20 remote monitored sessions lasting about 30 minutes each, carried out, on average, twice per week. No videos or photos of the patients will be acquired to guarantee the patient’s privacy and data confidentiality.

Patients will be evaluated in person after every 10 treatment sessions by the main author of the study, who is responsible for the surgical and postoperative follow-up of the study participants but blinded to group allocation.

Participants must complete a total of 4 face-to-face assessments to document the results:

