### Outcome measures

•
**Primary outcome:** Improvement of peripheral nerve regeneration of digital nerves in the hand measured using quantitative sensory tests (Semmes-Weinstein monofilaments and two-point discrimination tests measured and compared in the four presential assessments). The difference between the two treatment arms (group A × group B) measured through the sensory tests (SWM and 2PD) will be evaluated after randomization.•
**Secondary outcome:** Improvement of sensory functions and social participation of the individual submitted to neurorrhaphy of digital nerves of the hand measured through questionnaires (Cold Sensitivity Severity Scale described by
McCabe *et al.* (1991), and the Pain Disability Index questionnaire recommended by
Novak *et al.*, 2010).

**
*Semmes–Weinstein monofilament test (SWM).*
** The Semmes–Weinstein monofilament test is used to assess the perception of pressure thresholds, which reflect the reinnervation of peripheral targets. Using scored probes, the assessment of perception of touch/pressure is measured and recorded. This test is a prime marker of functional recovery and provides quantitative data that can be used to monitor the patient during the course of nerve regeneration (
Wang *et al.*, 2013).

Subjects were asked to place their hands over a table, and keep their eyes closed during this test. Each filament, starting with the smallest caliber, was tested over the pulp side of the affected finger. The filament was applied perpendicularly for 1 to 1.5 s in three trials. A positive response in at least 2 of the 3 trials marked the sensory threshold (
Gordon *et al.*, 2010). We used the test results for data analysis.

**
*Two-point discrimination test (2PD).*
** The two-point discrimination test, first described by WEBER in 1835 (
Dunlop *et al.*, 2019), is an established assessment tool for tactile gnosis (
Wang *et al.*, 2013). It is defined as the distance between compass points necessary for the patient to feel two contacts (
Rosén & Lundborg, 2000). Ideally, it is recorded as an absolute value compared to the corresponding portion of the contralateral, uninjured finger. Normal values in an undamaged strip of the finger vary from 2 to 6 mm (
Table 1).

**Table 1. T1:** Interpretation scale of the two-point discrimination test (reproduced from
Silva *et al.*, 2014).

Measurement	Interpretation
2 mm to 5mm	Normal
6 mm to 10 mm	Fair
11 mm to 15 mm	Poor
One point of perception	Protective

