### Sample size and patient allocation

Patient allocation and statistical analysis will be done by a researcher ([name]) who will be blinded to the procedures and groups. A simple randomization will be performed using sealed and opaque envelopes. There will be 16 patients per group (groups A and B), totaling 32 patients. The sample size is based on the study by
Gordon *et al.* (2010), as this is the only randomized clinical trial in the literature. We estimated the sample considering a repeated measures analysis of variance (ANOVA) test with interaction between and inter factors, with an effect size of 0.26 (according to
Gordon *et al.*, 2010), alpha-type error of 5%, power of 80%, two groups, three measures, with correction between factors of repeated measures of 0.5, and correction of non-sphericity of 1. These parameters resulted in 26 individuals in the total sample (13 per group), which were increased by 20% to compensate for possible losses, resulting in a final sample of 32 patients (16 per group). The selection of the sample to compose the two groups will be carried out by an experienced (>10 years) hand surgeon, through the clinical examination and application of evaluation tools (Semmes-Weinstein monofilaments, two-point discrimination tests, Cold Sensitivity Severity Scale and the Pain Disability Index).

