### Statistical analysis

All statistical tests will be performed using
SPSS (V25.0, IBM Corporation, New York, USA). The data will be evaluated in a paired and non-paired way. For paired evaluations (intra-group comparisons), repeated measures ANOVA or the Friedman test will be used, followed by the Student–Newman–Keuls post-test. For non-paired assessments (comparisons between groups), analysis of variance of a measure (one-way ANOVA or the Kruskal–Wallis test) will be used, followed by the Student–Newman–Keuls post-test. The choice of tests will depend on the normality or the nature of the data.

For statistical analysis, the 95% confidence interval will be considered, with an alpha of 5% (P < 0.05) and power of 80%. Descriptive analysis will be done through the averages or medians associated with the applicable dispersion measures (standard deviation or quartiles 25/75). Both the measurements of the variables in each study and the statistical analysis will be performed blindly.

The independent variable for both groups will be the use of electric currents. The dependent variables will be derived from the pre- and post-treatment assessments (Semmes-Weinstein monofilaments, two-point discrimination, Cold Sensitivity Severity Scale and Pain Disability Index).

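### The protocol gives conflicting times for collecting the two secondary questionnaires, so whether a pre-treatment score will exist is undetermined

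*Protocol article*

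**What the plan says.** Five places in the protocol article bear on when the Cold Sensitivity Severity Scale (CSS) and the Pain Disability Index (PDI) are collected.

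- **Data management:** "The Cold Sensitivity Severity Scale and Pain Disability Index questionnaires are applied to each participant in the last evaluation by the hand surgeon". No other time point is named.
- **Sample size and patient allocation:** the hand surgeon selects patients "through the clinical examination and application of evaluation tools (Semmes-Weinstein monofilaments, two-point discrimination tests, Cold Sensitivity Severity Scale and the Pain Disability Index". Selection precedes treatment.
- **Statistical analysis:** "The dependent variables will be derived from the pre- and post-treatment assessments", followed by a parenthesis naming all four instruments, CSS and PDI included. The section plans repeated measures ANOVA or Friedman tests within groups, and one-way ANOVA or Kruskal–Wallis tests between groups. No outcome is exempted from the paired tests.
- **Outcome measures:** the secondary outcome is "Improvement of sensory functions and social participation of the individual submitted to neurorrhaphy of digital nerves of the hand measured through questionnaires". The four-visit schedule is attached to the primary outcome alone: "Semmes-Weinstein monofilaments and two-point discrimination tests measured and compared in the four presential assessments".
- **Intervention (below Figure 1):** "Participants must complete a total of 4 face-to-face assessments to document the results". The visits are pre-intervention, one week after stimulation, after 10 sessions and after 20 sessions. The list does not say which instruments are used at which visit.

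**The concern.** Taken literally, these statements produce different datasets. Staff who work from Data management collect one CSS and one PDI score per patient, at the end. Staff who work from the Sample size or Statistical analysis section also hold a pre-treatment score. The planned within-group analysis and a within-patient reading of improvement need the second dataset.

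Social participation is one of the two specific aims under Objectives, and these questionnaires are its only stated measure. A score not taken before treatment cannot be recovered later. Study status says both that the trial will start after ethics approval and that it is at its treatment stage, so some patients may already be passing the early visits. The conflict also leaves the choice between change and final score open until the data exist.

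This is not detail that an article would normally leave to a fuller document. The article does state the timing, and it states it in ways that do not fit together.

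**Working it through.** **1. The plan's own figure.** The only stated calculation is the sample size, and it reproduces. Inputs from the Sample size section: f = 0.26, alpha 5%, power 80%, k = 2 groups, m = 3 measures, correlation 0.5, non-sphericity correction 1. For the group-by-time interaction:

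- λ = f² × N × m / (1 − 0.5) = 0.0676 × 26 × 3 / 0.5 = 10.55
- df1 = (k − 1)(m − 1) = 2; df2 = (N − k)(m − 1) = 48
- power = 0.811, and 26 is the smallest even N that reaches 0.80
- 13 × 1.2 = 15.6, rounded up to 16 per group, 32 in total

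The timing conflict changes none of this.

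**2. The statements side by side.**

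| Section | Implied CSS and PDI scores | Pre-treatment score? |
|---|---|---|
| Data management | last evaluation | none named |
| Sample size | at selection | taken, but not said to be kept as data |
| Statistical analysis | pre- and post-treatment | yes |
| Outcome measures | improvement; four visits tied to the two sensory tests only | not stated |
| Intervention | four visits, instruments not listed | not stated |

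No section ranks one statement over another.

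**3. What one score per patient permits.** With m = 1, (k − 1)(m − 1) = 0 and (N − k)(m − 1) = 0. There is no within-patient contrast to test, so neither the paired tests nor a change score exists. The between-group test on the final score remains available. For scale only, a two-sided 5% t test with 16 per arm has power of about 0.30, 0.59 and 0.78 at standardised differences of 0.52, 0.8 and 1.0. These differences are assumptions; the article gives no effect size for either scale.

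**4. What a pre-treatment score would add.** Let r be the correlation between the pre-treatment and final scores. Relative to the final score alone (variance 1), adjustment leaves 1 − r², and a simple change score has 2(1 − r). The effective sample multiplies by 1/(1 − r²).

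| r (assumed) | Adjusted: 1 − r² | Effective-sample factor | Change: 2(1 − r) |
|---|---|---|---|
| 0 | 1.00 | 1.00 | 2.00 |
| 0.3 | 0.91 | 1.10 | 1.40 |
| 0.5 | 0.75 | 1.33 | 1.00 |

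The 0.5 in the Sample size section is a general planning value for repeated measures and is not given for CSS or PDI. For r below 0.5 an unadjusted change score is less precise than the final score alone, which is why the fix uses adjustment and not subtraction.

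**The case against.** The strongest reply is that little of value is at risk. Data management names one time point but does not exclude others, and the surgeon applies both scales at selection. If those scores are kept, a pre-treatment value exists. Statistical analysis lists the four instruments together and defines no change score. Outcome measures also calls the primary outcome an improvement and then explains it as a difference between arms, so the word need not mean within-patient change. The paired within-group tests do not estimate the treatment effect in any case; the randomised comparison of final scores does, and it survives.

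Most of this stands, and it limits the point. A reader might infer that the secondary outcomes cannot be analysed at all, or that none of the 32 patients will have a pre-treatment score. The documents do not support either. The number with such a score could be anywhere from 0 to 32, depending on which section is followed and whether the selection scores are kept. A reader might also infer that the conflict costs the equivalent of a third of the sample. That needs r = 0.5 for these scales, which the article does not give, and a baseline-adjusted analysis, which it does not propose for any outcome. The CSS description says that cold sensitivity commonly develops after surgery and hand injury, and patients are operated on within two weeks of injury, so an early CSS score may predict the final one weakly.

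The reply does not remove the contradiction. Even if the questionnaires are meant for the end only, the Sample size section still conflicts, and the paired tests still have nothing to work on for these two scales.

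**Conclusion.** The protocol contradicts itself on when CSS and PDI are collected, and no section resolves it. The consequence is conditional: if Data management governs and the selection scores are not retained, within-patient improvement and the paired tests are unobtainable for both secondary outcomes. A between-arm comparison of final scores is valid on every reading. It estimates a difference between groups at the end, not recovery within patients.

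The precision at stake runs from nothing (r = 0) through about 10% (r = 0.3) to about 33% (r = 0.5) more effective patients, all on assumed correlations. The primary outcome and the sample size are unaffected. This should be fixed, and ideally before more patients pass the pre-intervention visit, but it does not threaten the trial's main conclusion.

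**What to change.** Make Outcome measures, Sample size, Data management and Statistical analysis give the same collection times, by one of two routes.

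1. **Preferred.** Record CSS (4 items) and PDI (7 items) at the pre-intervention assessment as well as the last one. Say in Data management that both scores are kept. Define the secondary endpoint for each scale as the difference between arms at the last assessment, adjusted for the pre-intervention score. The cost is a few minutes for 11 items at visits already planned, plus wording.
2. **Alternative.** If collection at the last visit only is intended, define the secondary endpoint as a between-arm comparison of final scores. Remove the word improvement and the paired tests for these two scales, take them out of the pre- and post-treatment list, and state that their use at selection, if kept, does not supply outcome data. The cost is wording only.

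If patients are already enrolled, first establish whether their selection scores were recorded, because that decides whether the first route is still open for them.

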### Statistical analysis

All statistical tests will be performed using
SPSS (V25.0, IBM Corporation, New York, USA). The data will be evaluated in a paired and non-paired way. For paired evaluations (intra-group comparisons), repeated measures ANOVA or the Friedman test will be used, followed by the Student–Newman–Keuls post-test. For non-paired assessments (comparisons between groups), analysis of variance of a measure (one-way ANOVA or the Kruskal–Wallis test) will be used, followed by the Student–Newman–Keuls post-test. The choice of tests will depend on the normality or the nature of the data.

For statistical analysis, the 95% confidence interval will be considered, with an alpha of 5% (P < 0.05) and power of 80%. Descriptive analysis will be done through the averages or medians associated with the applicable dispersion measures (standard deviation or quartiles 25/75). Both the measurements of the variables in each study and the statistical analysis will be performed blindly.

The independent variable for both groups will be the use of electric currents. The dependent variables will be derived from the pre- and post-treatment assessments (Semmes-Weinstein monofilaments, two-point discrimination, Cold Sensitivity Severity Scale and Pain Disability Index).

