## Abstract

We will study the influence of low intensity and frequency surface peripheral electrical stimulation (PES) on nerve regeneration of digital nerve injuries of the hand after its surgical repair in humans. Participants will be patients with acute traumatic peripheral nerve injury referred to the Hand Surgery Service of the General Hospital of the State of Bahia, a reference service in the state. These patients will undergo surgery followed by PES in the immediate postoperative period. After hospital discharge, they will be followed up on an outpatient basis by researchers, who will remotely supervise a physiotherapy program. Our hypothesis is that PES will positively influence the recovery of sensory function in patients undergoing neurorrhaphy of digital nerves of the hand.

**ReBEC registration:**  U1111-1259-1998 (12/18/2020)

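### The analysis plan lists within-arm tests over visits beside a between-arm test without saying which decides whether PES works, and omits the group × time interaction that sized the trial

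*Protocol article*

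**What the plan says.** All references are to the protocol article, the only document at hand.

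- **Hypothesis (Abstract):** "Our hypothesis is that PES will positively influence the recovery of sensory function in patients undergoing neurorrhaphy of digital nerves of the hand". The design is randomised and sham-controlled, so this is a comparative hypothesis.
- **Primary outcome (Outcome measures), first sentence:** "Improvement of peripheral nerve regeneration of digital nerves in the hand measured using quantitative sensory tests", with the Semmes-Weinstein (SWM) and "two-point discrimination tests measured and compared in the four presential assessments".
- **Primary outcome, second sentence:** "The difference between the two treatment arms (group A × group B) measured through the sensory tests" will also be evaluated.
- **Within-arm analysis (Statistical analysis):** "For paired evaluations (intra-group comparisons), repeated measures ANOVA or the Friedman test will be used", followed by a post-test.
- **Between-arm analysis (same section):** "For non-paired assessments (comparisons between groups), analysis of variance of a measure (one-way ANOVA or the Kruskal–Wallis test) will be used", with the same post-test. One 5% significance level applies to everything.
- **Sizing (Sample size and patient allocation):** a repeated measures ANOVA with an interaction, effect size 0.26, "alpha-type error of 5%, power of 80%, two groups, three measures", correlation 0.5. This gives 26 patients, raised to 32.

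**The concern.** The null hypothesis of the within-arm test is that nothing changes over the visits in that arm. Every participant starts with a transected digital nerve, has it repaired, and then has 20 sensory re-education sessions over three months. Some change is therefore to be expected in both arms whatever PES does, and rejecting that null says nothing about PES.

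The section confines repeated measures ANOVA to intra-group comparisons. The between-group test is a one-way test that does not model visits. The only stated procedure that uses the repeated assessments is thus the one that does not compare the arms. The first sentence of the primary outcome, improvement across four assessments, fits that procedure most directly.

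At stake is what a positive result would mean. With no deciding test named, significance in group A, or in group A but not in group B, could be offered as support for PES. The randomised control protects the conclusion only if a between-arm contrast decides it.

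**Working it through.** **1. The plan's own figure.** Inputs from the Sample size section: f = 0.26, k = 2 groups, m = 3 measures, ρ = 0.5, non-sphericity correction 1, α = 0.05. For the group × time interaction:

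- λ = f²·N·m/(1−ρ) = 0.0676 × 26 × 3/0.5 = 10.55
- df1 = (k−1)(m−1) = 2; df2 = (N−k)(m−1) = 48
- Power at N = 26 is 0.811. At N = 24 (λ = 9.73, df2 = 44) it is 0.775.

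So 26 is the smallest even total that reaches 80%, and 26 × 1.2 = 31.2 leads to 32. The stated numbers reproduce, which confirms that the trial was sized on the group × time interaction.

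**2. Which planned test answers which question.**

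| Test | Where stated | Uses the visits | Compares the arms |
|---|---|---|---|
| Group × time interaction | Sample size only | yes | yes |
| Repeated measures ANOVA or Friedman | Statistical analysis | yes | no |
| One-way ANOVA or Kruskal–Wallis | Statistical analysis | no | yes |

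**3. Within-arm test when PES has no effect.** Taken from the document: 16 per arm, four assessments, ρ = 0.5. Assumed: normal data with SD 1, and the same recovery in both arms, with means 0, 0, d/2, d over the four visits. The document gives neither a recovery size nor an SD, so d is varied.

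The mean over visits is 0.375d. The squared deviations sum to (2 × 0.140625 + 0.015625 + 0.390625)d² = 0.6875d². Hence λ = n × 0.6875d²/(1−0.5) = 1.375·n·d², which is 22d² for n = 16, with 3 and 45 degrees of freedom.

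The arms are independent. If p is the within-arm rejection rate, the pattern of significance in PES but not in sham has probability p(1−p), which cannot exceed 0.25.

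| d (SD) | λ | PES arm significant, noncentral F | Same, simulated | PES only, p(1−p) | Between-arm test, last visit, simulated |
|---|---|---|---|---|---|
| 0.25 | 1.375 | 0.135 | 0.134 | 0.117 | 0.051 |
| 0.5 | 5.5 | 0.444 | 0.444 to 0.450 | 0.247 | 0.050 to 0.052 |
| 0.8 | 14.08 | 0.868 | 0.864 | 0.115 | 0.048 |
| 1.0 | 22 | 0.976 | 0.976 to 0.977 | 0.023 | 0.048 to 0.050 |
| 1.5 | 49.5 | 1.000 | 1.000 | 0.000 | 0.048 |

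Simulations used 10,000 or 20,000 trials per setting. The sham arm has the same rates as the PES arm. The Friedman test gives 32%, 75%, 92% and 100% at 0.5, 0.8, 1.0 and 1.5 SD. With 13 completers per arm, the repeated measures ANOVA gives about 12%, 36%, 78%, 93% and 100% over the five values of d.

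**4. The between-arm alternatives.** Under the same null, the group × time interaction rejects in about 5% of trials for every d, as does the between-arm test at the last visit. If significance at any of the four visits were accepted, the rate would be about 16% per outcome. Calling for a between-arm test is therefore not enough; the analysis or the visit has to be named.

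**The case against.** The strongest reply is that the protocol does not rest on within-arm tests. The second sentence of the primary outcome names the difference between group A and group B, the Statistical analysis section plans a between-group test, and the sample size assumes two groups and an interaction. Nowhere does the document say that significance in group A, or in one arm only, counts as success. That stands. A reader might infer that the primary outcome is tested only within arms, or that the trial will come out positive almost every time even if PES is inert. The document supports neither reading. The between-arm comparison is stated, and the high rates need recovery approaching 1 SD or more, which is an assumption.

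It also stands that the two possible misreadings do not peak together. The pattern of PES significant and sham not is most frequent near 0.5 SD, where the PES-arm test is positive in under half of trials. Where that test is nearly always positive, the pattern almost disappears. The normal model is also only approximate for two-point discrimination, whose interpretation scale has non-numeric grades.

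A further reply is that ranking the tests can be left to a statistical analysis plan that is not shown. This answers only part of the point. The article itself sets out inferential within-arm tests, restricts repeated measures ANOVA to them, and lists an analysis set without the interaction on which its own sample size depends. These are stated choices, not details left for later.

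**Conclusion.** The concern holds in this limited form. The plan gives within-arm tests over visits and a separate between-arm test the same 5% level, names neither as deciding, and drops the interaction that produced N = 26. The wording of the primary outcome leaves room to read a within-arm result as evidence for PES.

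The size of the problem depends on the recovery common to both arms. At 0.25 SD the within-arm test would be significant in an inert PES arm in about one trial in eight. From about 1 SD it would be so in nearly all. A between-arm test at one named visit, or the interaction, holds its 5% level throughout. These figures rest on normal data, a correlation of 0.5, equal recovery in both arms and the assumed path over visits. The qualitative conclusion needs none of these: a test that does not compare the arms cannot attribute change to PES.

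**What to change.** - **Outcome measures:** define the primary outcome as the group A versus group B contrast in SWM and two-point discrimination, so that improvement over visits is no longer its first description.
- **Statistical analysis:** name one between-arm analysis as deciding, reported with its 95% confidence interval. This can be the group × time interaction on which the trial was sized, or a baseline-adjusted A-versus-B difference at one stated visit. If the interaction is chosen, state which visits enter it, because the sample size counts three measures and four assessments are planned.
- **Within-arm results:** report them descriptively (mean or median with spread at each visit), and state that significance within group A, or in one arm only, is not evidence for PES.

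The cost is a wording change in two sections, with no new patients or data. The only loss is that within-arm P values are no longer reported. If a baseline-adjusted difference is chosen instead of the interaction, the sample size justification should be restated for that analysis.

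### Student-Newman-Keuls does not in general control the familywise error over four visits: the worst case is about 10% per arm and sensory test

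*Protocol article*

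**What the plan says.** The Statistical analysis section separates within-arm from between-arm comparisons. Within an arm, "repeated measures ANOVA or the Friedman test will be used, followed by the Student–Newman–Keuls post-test". Between arms, one-way ANOVA or Kruskal–Wallis is named, again with Student-Newman-Keuls as the post-test. The level is given once, "with an alpha of 5% (P < 0.05) and power of 80" per cent, and is not described as familywise or per comparison. No other multiplicity adjustment for the visit comparisons is stated.

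The number of means is also fixed. The Intervention section says "Participants must complete a total of 4 face-to-face assessments to document the results": before stimulation, one week after it, after 10 rehabilitation sessions and after 20. The Outcome measures section says that the two primary sensory tests, SWM and 2PD, are "measured and compared in the four presential assessments". On group size, "There will be 16 patients per group (groups A and B), totaling 32 patients".

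**The concern.** A post-test after an omnibus test usually has one purpose: to limit the chance of a false finding over the whole set of pairwise comparisons. Four visits give six pairs in each arm for each sensory test. Student-Newman-Keuls lowers its critical value as the span of ordered means shrinks, so a neighbouring pair is tested at the full 5%. When more than one neighbouring pair is truly equal and the wider spans are significant for good reason, these 5% chances add up.

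In this trial the first two visits (before stimulation and one week later, after a transected nerve has been repaired) could well be equal. If the last two visits are equal as well, the pattern that breaks the procedure is present. What is at stake is the reliability of statements about which visits differ within an arm. These could include a difference between the first two visits, or between the last two, that is not real.

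**Working it through.** **Inputs from the protocol.** Four assessments (Intervention); SWM and 2PD compared at all four (Outcome measures); alpha 5% and Student-Newman-Keuls (Statistical analysis); 13 evaluable and 16 enrolled patients per arm, and a correlation of 0.5 between repeated measures (Sample size and patient allocation).

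**The plan's own figure.** The sample size is computed "with an effect size of 0.26" and "alpha-type error of 5%, power of 80%, two groups, three measures, with correction between factors of repeated measures of 0.5". For the group-by-time interaction, λ = f²·N·m/(1 − ρ) = 0.26² × 26 × 3 / 0.5 = 10.55, with df = (2 − 1)(3 − 1) = 2 and (26 − 2)(3 − 1) = 48. The power is 0.811 at N = 26 and 0.794 at N = 25, so 26 reproduces. The loss allowance gives 26 × 1.2 = 31.2, taken up to 32, or 16 per arm. This step supports the use of 13 and 16 patients below. The calculation concerns the interaction and gives no assurance about the post-test.

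**Formula for the worst case.** Suppose visits 1 and 2 share one mean, visits 3 and 4 share another, and the two levels are well apart. The spans of four and three means are then significant because of the real difference, and the procedure goes on to test each equal pair at 5%. The two pair differences are close to independent, so

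familywise error = 1 − (1 − 0.05)² = 1 − 0.9025 = 9.75%.

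**Simulation of the full step-down procedure.** The set-up was one arm, four visits, normal data with unit SD at each visit, correlation 0.5, sphericity, the residual mean square from the repeated measures ANOVA, and 60,000 runs per cell. Each cell shows the percentage of runs with at least one false difference, with / without a significant overall F required first.

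| True visit means (in SD) | n = 13 | n = 16 |
|---|---|---|
| 0, 0, 0, 0 | 4.40 / 5.03 | 4.27 / 4.99 |
| 0, 0, 0, 3 | 5.08 / 4.90 | 5.12 / 4.82 |
| 0, 0, 0.5, 0.5 | 6.95 / 7.04 | 7.67 / 7.56 |
| 0, 0, 1, 1 | 9.85 / 9.59 | 9.68 / 9.59 |
| 0, 0, 3, 3 | 9.61 / 9.60 | 9.55 / 9.68 |
| 0, 0, 6, 6 | 9.71 / 9.81 | 9.88 / 9.63 |

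The Monte Carlo standard error near 9.75% is √(0.0975 × 0.9025 / 60,000) = 0.12 percentage points. Requiring a significant F first does not help, because the real difference between the pairs makes F significant.

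**Continuing recovery.** With 16 patients and correlation 0.5, means of 0, 0, 2, 3 and of 0, 0, 2, 2.5 each gave 5.0%. Only one true null remains in these patterns, so there is nothing to accumulate.

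**Alternatives in the bad pattern.** Under Holm, once the four real differences are rejected, the smaller of the two remaining p-values is compared with 0.05/2. The chance of a false difference is about 1 − (1 − 0.025)² = 4.94%. Tukey's procedure, with means of 0, 0, 4, 4, gave 2.1%. Holm therefore holds the level and is less conservative than Tukey in this pattern.

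**The case against.** The strongest reply is that the 10% needs a special pattern. Assessments 3 and 4 are 10 sessions apart at about two a week, so roughly five weeks of re-education separate them. Nothing in the protocol says that recovery is complete after session 10. If it continues, the error rate is 5%. This stands, and it is why 10% is a worst case and not the rate to expect. It does not rescue the procedure, because a post-test is chosen before the pattern of means is known and should hold its level under any of them.

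Four stronger readings are tempting and are not supported:

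- **The protocol contradicts its own 5%.** The 5% is not called familywise, and even in the bad pattern each pair is tested at 5%. Reading it as the rate for the set follows the usual purpose of a post-test. It is an interpretation and not the document's wording.
- **Every outcome is affected.** The Data management section places the cold sensitivity and pain disability questionnaires in the last evaluation. The Statistical analysis section speaks of pre- and post-treatment assessments. Neither establishes four visits for them. The point is limited to SWM and 2PD.
- **The treatment comparison is inflated.** Two arms give one pair. Student-Newman-Keuls inflates nothing there; it is merely redundant.
- **Naming it after Friedman or Kruskal–Wallis is an error.** Step-down comparisons of this type can be made on rank sums, so the wording is imprecise and not demonstrably wrong.

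It can also be said that strict control matters little for contrasts that do not answer the trial's question. That is fair, and it keeps the point minor.

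**Conclusion.** The concern holds in limited form. For the within-arm visit comparisons of SWM and 2PD, the named post-test does not guarantee a 5% familywise error. The worst case is about 10% per arm and test, when two separate pairs of visits are equal and the pairs lie 1 SD or more apart. It is about 7–8% at 0.5 SD, and about 5% when all visits are equal, when three are equal, or when recovery continues between the last two visits.

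These figures assume normal data, sphericity and a correlation of 0.5. The Friedman branch was not simulated; the same two-pair reasoning applies to it, but no figure is given for it here. A reader should not conclude that the test of stimulation against sham is compromised, since that comparison is untouched. This is a low-severity improvement to a method that the protocol fixes in its own text.

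**What to change.** In the Statistical analysis section:

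1. Replace Student-Newman-Keuls for the visit comparisons with Holm-adjusted paired comparisons: paired t-tests after repeated measures ANOVA, Wilcoxon signed-rank tests after Friedman.
2. Say that the 5% applies familywise to the set of visit comparisons within each arm and sensory test.
3. Delete the post-test after the two-arm comparison.
4. State that within-arm visit contrasts are descriptive and are not evidence of a stimulation effect. This guards against reading a significant change in one arm and a non-significant one in the other as a difference between arms.

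The cost is wording only, with no change to visits, data or sample size. The downside is slightly less power for the within-arm contrasts.
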